### Implementation strategies

#### Educational strategy

The educational strategy is a full-day educational meeting (6.5 h) held at two occasions in October 2017, once for each of the participating municipalities. One of the meetings is held at the university and the other at the city hall. Prior to the meeting school principals receive an invitation by email describing the purpose of the meeting and the requirements for participation. The requirements include forming a group of 4–5 individuals (e.g. teacher union representatives, teacher representatives, health and safety officers, assistant school principals), discussing with the group the current approach to the management of social and organizational risk factors at their school and participating in the meeting with the group. Two members of the research team (a researcher with implementation expertise and a licensed psychologist with occupational health expertise) hold the educational meeting. At the start of the meeting, participants receive the *Guideline for the prevention of mental ill-health at the workplace* and a compendium, which includes handouts of the presentations and documents related to the planned exercises. The educational meeting includes PowerPoint presentations, material for plenary discussions and group-exercises. Table 3 provides an overview of the content of the educational meeting and the constructs of the COM-B they are targeting. The programme theory for the implementation strategies is depicted in Fig. 2.

#### Implementation team

Directly after the educational meeting in October 2017 school principals are instructed to form an implementation team among those individuals who participate in the educational meeting (3–5 individuals). The implementation team is responsible for leading the implementation of the guideline within their own school during the study period and beyond. To facilitate the implementation process, implementation teams use *Plan-Do-Study-Act* improvement cycles [41]. During *Plan* the implementation team specifies the action-plan to implement a guideline recommendation within their school (one recommendation at a time). During *Do* the implementation team carries out the action-plan as specified. During *Study* the implementation team assesses whether the action-plan was executed as planned and which factors influenced execution. During *Act* the implementation team makes changes to the plan, if needed, to further improve implementation. The implementation team repeats the *Plan-Do-Study-Act cycles* until the chosen recommendation is implemented and then continues with a new *Plan-Do-Study-Act cycle* for the next recommendation. In addition, implementation teams are responsible for establishing a communication plan specifying how they will communicate with their municipality’s educational board during the implementation process. Table 3 describes the relationship between the implementation team and the constructs of the COM-B model. Implementation teams receive support through a series of five workshops.

#### Workshop series

At each of the municipalities, the research-team holds a series of five workshops (2.5 h per workshop) for the implementation teams (October 2017–June 2018). The first workshop is given 2 weeks after the educational meeting. A researcher with implementation expertise and a licensed psychologist with occupational health expertise give the first three workshops; the same researcher with implementation expertise and a researcher with expertise in the guideline recommendations give the last two workshops. The workshops provide the implementation teams with knowledge and skills regarding 1) the recommendations of the guideline, 2) implementation processes, and 3) *Plan-Do-Study-Act cycles*. During workshop 1 the research team presents recommendation 1 and specified target-behaviors, during workshop 2 recommendation 2 and specified target-behaviors are presented, during workshop 3 the research team presents routines for how to sustain implemented changes over time, during workshop 4 and 5 recommendation 3 and specified target-behaviors are presented. With regards to the implementation process the research team presents the concept of SMART-goals (Specific, Measurable, Achievable, Relevant and Time-bound), behavior change and barriers and facilitators that can influence behavior change, and strategies needed to target the identified barriers and facilitators. Moreover, implementation teams work with their *Plan-Do-Study-Act* cycles: developing a detailed plan for implementing the recommendations (*Plan),* discussing the success of carrying out their plan (*Study*), and adapting the plan if necessary (*Act*). In between the workshops, implementation teams carry out the action-plan as specified (*Do*). Every workshop includes PowerPoint presentations, plenary discussions and group-exercises. At the start of each workshop, participants receive a compendium, which includes handouts of the presentations and documents related to the planned exercises.

Documents for workshop 1 and 2 include worksheets to form SMART-goals, A4-sized papers to write down the different steps towards reaching the goal and empty action plans to fill in. Documents for workshop 3 include written information on routines, the formulation of routines and examples of existing routines in this field, and a worksheet on which the implementation team can formulate their own routine. Documents for workshop 4 include a detailed description of recommendation 3, including an example of how to schedule a meeting at the workplace to discuss and prioritize identified social and organizational risk factors. Moreover, empty action plans are provided. Documents for workshop 5 include empty action plans. Additional documents for workshop 2–5 include A3-sized *Plan-Do-Study-Act* cycles, on which the research-team notes the implementation teams’ progresses. Table 3 provides an overview of the content of the workshops and the constructs of the COM-B they are targeting.

### Criteria for discontinuation and monitoring

It is not possible to modify the allocated implementation strategies for a given school. Individual participants can discontinue their participation during the study trial and have their results removed. Two persons from the research-team will deliver the intervention strategies to the schools, reminding each other to adhere to the protocol. Detailed schedules for the educational-meeting and for each workshop are developed to further improve adherence to the protocol. The schedule includes a description of the time line, different components (e.g. group work, presentation) and who is responsible for which components. The schedule includes a fidelity column where any deviations are noted. The research-team will be responsible for monitoring whether the implementation interventions are delivered according to the protocol. Procedures for monitoring adherence include making notes in the fidelity column when deviations occur, for example regarding time or content. Moreover, a research-log is kept describing deviations and possible reasons for deviations.

### Contamination care

To reduce the risk of contamination between schools of ARM 1 and 2 within the same municipality, schools of ARM 1 are encouraged not to discuss the project with schools of ARM 2. Every 6 months during the trial period, the research team has a telephone meeting with the school principals to collect data regarding schools’ exposure to other interventions and potential contamination for control schools.

### Outcomes

An overview of the measurement variables, method of data-collection, data-source and time-point for each measure is described in Table 4.

**Table 4 Tab4:** Measurement variables, method of data-collection, data-source and time-points

Measure	Method of data collection	Data source	Time-point
Demographic data			
*1. Implementation effectiveness*			
Guideline adherence	Questionnaire (developed by research team)	School management, school personnel	T0, T1, T2, T3 and T4
*2. Intervention effectiveness*			
Demands at work -Quantitative demands -Work pace -Emotional demands	Questionnaire (COPSOQ-II [42])	School management, school personnel	T0, T1, T2, T3 and T4
Work organization and job contents -Influence -Possibilities for development -Commitment to the workplace	Questionnaire (COPSOQ-II [42])	School management, school personnel	T0, T1, T2, T3 and T4
Interpersonal relations and leadership -Social support from superior -Social support from colleagues -Recognition	Questionnaire (COPSOQ-II [42])	School management, school personnel	T0, T1, T2, T3 and T4
Presenteeism	Questionnaire [43]	School management, school personnel	T0, T1, T2, T3 and T4
Work performance	Questionnaire (WPAI:GH [44, 45])	School management, school personnel	T0, T1, T2, T3 and T4
Need for recovery	Questionnaire [46]	School management, school personnel	T0, T1, T2, T3 and T4
Work-life balance	Questionnaire (COPSOQ-II [42])	School management, school personnel	T0, T1, T2, T3 and T4
Work engagement	Questionnaire (UWES [47])	School management, school personnel	T0, T1, T2, T3 and T4
Stress	Questionnaire [48]	School management, school personnel	T0, T1, T2, T3 and T4
	Mobile-phone text message-question [49]	School management, school personnel	Monthly during 12 months
Self-perceived health	Questionnaire (SF-12 health [50])	School management, school personnel	T0, T1, T2, T3 and T4
Short-term sick leave	Questionnaire [45]	School management, school personnel	T0, T1, T2, T3 and T4
Long-term sick leave due to mental ill-health	Register-data Swedish Insurance Agency	School management, school personnel	1-year before baseline and during the study period
Exhaustion	Questionnaire (OLBI [51])	School management, school personnel	T0, T1, T2, T3 and T4
Psychosocial safety climate	Questionnaire (PSC [52])	School management, school personnel	T0, T1, T2, T3 and T4
*3. Implementation process*			
Reach	Participation list	Research team	During the educational meeting and workshops
Acceptability	Interview	Implementation team members	T2, T4
Feasibility	Interview	Implementation team members	T2, T4
Satisfaction	Questionnaire	Participants educational meeting, workshops	After the educational meeting, after each workshop
	Interview	Implementation team members	T2, T4
Fidelity	Observation, meeting notes, work documents	Research team	During educational meeting and workshops
Barriers and facilitators	Interview (CFIR [21])	Implementation team members	T2, T4

T0: Baseline, T1: 6 months after baseline, T2: 12 months after baseline, T3: 18 months after baseline and T4: 24 months after baseline.

### Timeline of the enrolment, implementation strategies and assessments

Figure 3 describes the time schedule of enrolment, implementation strategies and assessments.

**Fig. 3 Fig3:**
[figure not shown]
Time schedule of enrolment, implementation interventions and assessments

### Sample size

The power-calculation for the proposed study is calculated on the effectiveness on employee-level (intervention effectiveness). In order to achieve 80% statistical power and a significance level of *p* < 0.05 to be able to detect an improvement in the primary outcome exhaustion with 30% among employees in the intervention group compared with employees in the control group, an intra-cluster correlation has been weighted (ICC = 0.005) and about 400 people in total are required (200 people in the intervention group and 200 people in the control group). This required the participation of at least 18 schools.

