### Trial design

The study is a 12-month cluster-randomized waiting list-controlled trial with before and after measurements involving 20 primary schools in two municipalities in Sweden. Randomization (1:1 allocation to intervention and waiting list control) is conducted at the school level. Primary schools are randomized by a computer-generated randomization-list to either the ARM 1 or ARM 2 after stratification in blocks by municipality and school size (number of students per school). Schools in ARM 1 will receive all three implementation strategies during the first year of the study period while schools in ARM 2 will receive only the educational strategy in year 1 and continue with the other strategies during year 2 (Fig. 2). The implementation strategies target the managerial level of first line managers i.e. school-principals. All employees of the participating schools will be invited to complete outcome-questionnaires at baseline and 6-, 12-, 18- and 24-months follow-up during working hours.

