##### Outcome measures (intervention effectiveness)

Primary outcome

The primary outcome is exhaustion (intervention effectiveness). Change from baseline in self-reported exhaustion during 6-, 12-, 18- and 24-months follow-up is assessed by the same questionnaire as described above. We hypothesise that adherence to the recommendations of the guideline will reduce self-reported exhaustion assessed with the exhaustion scale of the Oldenburg Burnout Inventory (OLBI) [51]. Six items of the inventory are used with answering categories ranging from (1) “strongly agree” to (4) “strongly disagree”.

Secondary outcomes

The following secondary outcomes are assessed at baseline and at 6, 12, 18 and 24 months with the same questionnaire as described under implementation effectiveness directed at the school-management and school-personnel. Long-term sick-leave is assessed by register-data from the Swedish Social Insurance Agency. An overview of each secondary outcome and a description of the items used is given below.

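### The 30% improvement in exhaustion does not fit 80% power with about 400 people on the outcome as defined; the target effect needs restating on the scale of the primary analysis

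*Protocol article*

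**What the plan says.** The *Sample size* section of the protocol article bases power on the employee-level outcome. It opens "In order to achieve 80% statistical power and a significance level of" 0.05, and gives the target as being "to be able to detect an improvement in the primary outcome exhaustion with 30% among employees in the intervention group compared with employees" of the control arm. It continues: "an intra-cluster correlation has been weighted (ICC = 0.005) and about 400 people in total are required", split as "200 people in the intervention group and 200 people in the control group", and adds "This required the participation of at least 18 schools". The *Trial design* section describes a trial "involving 20 primary schools in two municipalities in Sweden".

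The section does not say what the 30% is a percentage of. It gives no mean, SD, proportion, cut-off or time point.

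Under *Outcome measures (intervention effectiveness)*, the primary outcome is change from baseline in OLBI exhaustion: "Six items of the inventory are used with answering categories ranging from" 1 to 4. *Statistical methods* tests the between-group difference in exhaustion with mixed effects regression. No dichotomised exhaustion outcome is defined anywhere in the article.

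**The concern.** For a score with a continuous analysis, the plain meaning of a 30% improvement is a mean 30% lower than in the control group. On a scale that starts at 1, the mean is large relative to the spread, so 30% of it is a large standardised effect. A large effect needs far fewer than 400 people. The effect, the power and the sample size stand in one sentence but do not appear to belong together.

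This is the only target effect the article gives for its primary outcome, so readers will judge the result against it. If the design in fact targets a difference several times smaller in relative terms, a null result will be misread. A positive result of the size actually planned for may be dismissed as falling short.

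**Working it through.** **Inputs from the article:** power 80%, significance level 0.05, ICC 0.005, 200 per arm, at least 18 schools (20 planned), items scored 1 to 4. **Assumptions:** two-sided test, equal cluster sizes, no dropout allowance, no gain from baseline adjustment or repeated measures.

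**Design effect.** With 18 schools, 400/18 = 22.2 people per school, and 1 + 21.2 × 0.005 = 1.106. With 20 schools, 1 + 19 × 0.005 = 1.095.

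**Can the stated 400 be reproduced?** Not from the stated inputs alone, because the reference for the 30% is missing. Each reading is therefore tried in turn.

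*Reading A: standardised difference of 0.30.*
- n per arm = 2 × (1.96 + 0.8416)² / 0.30² = 174.4.
- Total with 18 schools = 2 × 174.4 × 1.106 = 386, or 388 when each step is rounded up. With 20 schools it is 384.
- Power with 200 per arm is 81 to 82%.
- Smallest difference detectable with 80% power and 18 schools = 2.80 × √(2 × 1.106/200) = 0.295 SD.
- This fits about 400.

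*Reading B: mean score 30% lower, items scored 1 to 4.*
- For any distribution on 1 to 4 with mean μ, the SD cannot exceed √((μ − 1)(4 − μ)).
- SD/μ is largest at μ = 1.6, where the SD limit is √(0.6 × 2.4) = 1.2 and the ratio is 1.2/1.6 = 0.75.
- 30% of 1.6 is 0.48, and 0.48/1.2 = 0.40. So a 30% lower mean is at least 0.40 SD.
- n per arm = 2 × 2.8016² / 0.40² = 98.1, rounded up to 99. Then 99 × 1.106 rounds up to 110 per arm, or 220 in total.
- Power with 200 per arm: the effective n is 200/1.106 = 180.8, and 0.40 × √(180.8/2) − 1.96 = 1.84, which gives about 97%.
- That is the extreme case. With assumed SD/mean ratios of 0.20, 0.30 and 0.50, the totals are 16, 36 and 98.
- Reaching about 400 would need a ratio of 1.0, above the limit of 0.75. This reading does not fit.

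*Reading C: 30% relative change in a proportion* (18 schools, design effect 1.106, control rates assumed).

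| Control → intervention | n per arm before clustering | Total |
|---|---|---|
| 30% → 21% | 367 | 812 |
| 40% → 28% | 244 | 540 |
| 48% → 33.6% | 182 | 404 |
| 50% → 35%, continuity correction | 183 | 406 |
| 48.5% → 63.1% (more people improved) | 182 | 404 |

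The 48% row gives 396 if the variance is not pooled under the null hypothesis. The first two rows keep the design effect at 1.106; with only 18 schools and larger clusters they would be higher. This reading fits, but only near a control rate of 48 to 50%.

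*Reading D: 30 percentage points.* Totals are about 50 to 96. This does not fit.

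**What Reading A would mean on the scale.** With an assumed SD of 0.5 to 0.7, 0.30 SD is 0.15 to 0.21 points. Against an assumed mean of 2.3, that is 0.15/2.3 = 6.5% to 0.21/2.3 = 9.1%, not 30%.

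**The case against.** The strongest reply is that 400 has not been shown to be wrong. The wording is open to a proportion reading, and a 30% relative reduction from about 48% reproduces the figure as well as 0.30 SD does. The article never mentions a standardised effect, and a value that fits is not evidence of what was entered. This stands. A reader might infer that the figure can only have come from 0.30 SD written as a percentage. The documents do not support that.

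The 0.40 SD bound also has limits. It holds for a mean or sum of items scored 1 to 4. It does not cover a 30% difference in change scores or a score rescaled to start at 0. On a 0 to 3 scoring with an assumed mean of 0.7 and SD of 0.7, 30% of the mean is 0.30 SD and the total is again about 386. So the claim that a 30% reduction can never give 400 would be too strong. However, the article describes neither a rescaled score nor a power calculation on percentage change.

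Finally, an article condenses a fuller protocol, and the missing SD or control rate may be recorded elsewhere. That is fair, and the absence of those inputs is not the point. The article itself puts an effect, a power and a sample size side by side, and they do not match on the outcome and analysis it describes.

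**Conclusion.** The concern holds in a limited form. On exhaustion scored 1 to 4, a 30% difference in means needs at most about 220 people at ICC 0.005. With 200 per arm it has about 97% power or more, so 80% is not the power that 400 people give for that effect. Baseline adjustment or repeated measures would normally widen the gap.

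Each reading that does give about 400 leaves a mismatch with the plan. Either 30% is the wrong figure for the stated score, or the power was computed for a dichotomised or differently scored outcome that the article neither defines nor analyses. Which of these applies cannot be told from the document.

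A reader might also infer that the trial is too small. Nothing here shows that: if the target is 0.30 SD, 400 people suffice under the stated ICC. The defect lies in the stated target effect. Confidence is moderate, and the result rests on the assumptions listed with the calculation.

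**What to change.** The sponsor should go back to its power calculation, establish what the 30% referred to, and restate the target effect so that it matches the primary analysis.

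- If it was a standardised difference, replace the 30% with 0.30 SD, and give the SD used and the equivalent difference in scale points.
- If it was a proportion, give the cut-off and the assumed control rate. Then either align the primary analysis with that outcome, or restate the detectable difference for the continuous score (about 0.29 SD with 200 per arm and 18 schools).
- If another scoring or a change score was used, state it with its mean and SD.

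Neither 0.30 SD nor a particular follow-up time should be written in by default, because the sample size section names neither. The cost is one sentence and a less striking target; the sample size need not change.

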## Methods

### Assignment of interventions

#### Allocation

Primary schools are randomized to either ARM 1 or ARM 2 after stratification in blocks by municipality and school size (number of students per school). This is done by a computer-generated randomization-list. Randomization is conducted prior to the baseline measurement due to logistical reasons, as the educational meeting and workshops needed to be scheduled so that they fit with the individual planning of each school. An independent statistician, blind to the identity of the schools and not involved within the project, conducts the randomization. The project leader informs the educational board of the municipalities and the school principals by e-mail about their allocation. After assignments to implementation strategies, neither the school management or school personnel are blinded.

### Data collection, management and analysis.

#### Data collection methods.

##### Outcome measures (implementation effectiveness)

The outcome measure of implementation effectiveness is guideline adherence. Change from baseline in adherence to the recommendations of the guideline during 6-, 12-, 18- and 24-months follow-up period are measured by questionnaire. Two questionnaires are used, one directed at the school management and one directed at the school personnel. The questionnaires are developed by the research team for the purpose of this study in order to fit with the guideline’s recommendations and can be obtained upon request from the corresponding author. In order to promote participation retention and complete follow-up, the research team hands out the questionnaires in paper form in individual envelops to school personnel during the participating schools’ regular staff meetings. During these meetings, school-personnel complete the questionnaires during working hours, which they return directly to the research team on completion. A representative of the research-team is present until all questionnaires are retrieved, in order to answer questions and explain the procedure. An electronic version of the paper-questionnaire is sent to those individuals who are not present at the meeting. Three reminders are sent to those participants not responding, with 1-week interval. No outcome-data are collected from participants who discontinue. The participants do not receive a remuneration for completing the questionnaires.

The school management ((assistant) - school-principal) complete a questionnaire containing statements related to the guideline’s recommendations. Nine items (5-point Likert Scale: “fully disagree”- “fully agree”; and do not know) are used to assess adherence to recommendation 1: *Workplaces should have well-established policies related to the social and organizational risk management* (e.g. The introduction of new employees includes a briefing of the school’s working environment document). Adherence to recommendation 2: *Employers should have knowledge on the relationship between social and organizational risks and mental ill-health* is assessed with five items (5-point Likert Scale: “fully disagree”- “fully agree”; and do not know) (e.g. We have written documents stating what the school-management needs to know regarding how the work environment affects mental ill-health). Ten items are used to assess adherence to recommendation 3: *Workplaces should regularly assess their social and organizational work environment and intervene on identified social and organizational risk factors* (5-point Likert Scale: “fully disagree”- “fully agree”; and do not know) (e.g. In the last assessment of social and organisational risk factors at the workplace, the school management and employees together developed an action plan for improvement of identified social and organisational risks at the workplace). Moreover, one item (multiple-choice) assesses when the last assessment of the social and organisational work environment had taken place.

School-personnel complete a questionnaire containing similar statements related to the guideline’s recommendations as those described above. Three items are used to assess adherence to recommendation 1: *Workplaces should have well-established policies related to the social and organizational risk management* (e.g. I am familiar with the content of our work environment documents). Adherence to recommendation 2: *Employers should have knowledge on the relationship between social and organizational risks and mental ill-health* is assessed with one item. Nine items are used to assess adherence to recommendation 3: *Workplaces should regularly assess their social and organizational work environment and intervene on identified social and organizational risk factors* (e.g. In the last assessment the activities specified in the action-plan led to noticeable improvements in the social and organizational work environment). Moreover, one item (multiple-choice) assesses when the last assessment of the social and organisational work environment took place.

